# TREATMENT OF SUBJECTS

Not applicable

## Investigational product/treatment

## Use of co-intervention (if applicable)

## Escape medication (if applicable)

# INVESTIGATIONAL PRODUCT

Not applicable.

## Name and description of investigational product(s)

## Summary of findings from non-clinical studies

## Summary of findings from clinical studies

## Summary of known and potential risks and benefits

## Description and justification of route of administration and dosage

## Dosages, dosage modifications and method of administration

## Preparation and labelling of Investigational Medicinal Product

## Drug accountability

# NON-INVESTIGATIONAL PRODUCT

Not applicable

## Name and description of non-investigational product(s)

## Summary of findings from non-clinical studies

## Summary of findings from clinical studies

## Summary of known and potential risks and benefits

## Description and justification of route of administration and dosage

## Dosages, dosage modifications and method of administration

## Preparation and labelling of Non Investigational Medicinal Product

## Drug accountability

# METHODS

## Study parameters/endpoints

Farmacokinetic parameters (i.e. clearance, AUC)

### Main study parameter/endpoint

Farmacokinetic parameters (i.e. clearance, AUC)

### Secondary study parameters/endpoints (if applicable)

Not applicable

### Other study parameters (if applicable)

Not applicable

## Randomisation, blinding and treatment allocation

Not applicable

## Study procedures

Pharmacokinetic sampling

Fentanyl pharmacokinetics will be performed with a single blood sample during stable dosing.. One blood sample (4.5 mL) will be drawn through a cannula from a vein in the arm (**opposite to the one where the fentanyl patch is placed**). The blood sample will be collected in the presence of potassium EDTA as anticoagulant and will be processed to plasma within 10 minutes by centrifugation for 10 min at 2,500-3,000*g at 4°C. Plasma will be transferred into polypropylene tubes (1.8 mL Nunc vials), which will be stored at T<-70°C (T<-20°C during collection period) until time of analysis.

Pharmacokinetic data analysis

All fentanyl drug concentrations will be measured at the Laboratory of Translational Pharmacology of the Erasmus MC, Rotterdam by the use of a validated mass-spectometry (LC-MS/MS) assay.

Pharmacokinetic data analysis will take place using WinNonlin or other an appropriate method to calculate exposure measures (i.e. CL) at the Laboratory of Translational Pharmacology of the Erasmus MC, Rotterdam.

## Withdrawal of individual subjects

Subjects can leave the study at any time for any reason if they wish to do so without any consequences. The investigator can decide to withdraw a subject from the study for urgent medical reasons.

### Specific criteria for withdrawal (if applicable)

Not applicable

## Replacement of individual subjects after withdrawal

In this study we will include a maximum of 80 evaluable patients (due to a maximum of financial recourses).

## Follow-up of subjects withdrawn from treatment

Not applicable

## Premature termination of the study

Not applicable.

# SAFETY REPORTING

Not applicable

## Section 10 WMO event

## AEs, SAEs and SUSARs

### Adverse events (AEs)

### Serious adverse events (SAEs)

### Suspected Unexpected Serious Adverse Reactions (SUSAR's)

## Annual safety report

## Follow-up of adverse events

## [Data Safety Monitoring Board (DSMB) / Safety Committee]

Not applicable.

# STATISTICAL ANALYSIS

The clearance of all different samples is calculated. This is independent of the dose because of linear pharmacokinetics. After this calculation we will use the Student’s t test to compare the clearance for fentanyl in patients with a BMI < 20 compared to a BMI > 25 and for smokers versus non-smokers.

For all 4 of these groups at least 20 patients have to be included.

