# INTRODUCTION AND RATIONALE

Pain is a common problem in cancer patients, occurring both in curative settings as well as in palliative settings. Opioids are often used to treat cancer pain. Fentanyl is one of the most widely used opioids.

Several preparations of fentanyl are currently available . The transdermal fentanyl patch is developed for maintenance medication in chronic pain and is the most commonly used form. Patches are available in different sizes, consistent with specific delivery doses of these patches (12ug/hr, 25ug/hr, 50ug/hr, 75ug/hr or 100ug/hr). Fentanyl is absorbed through the intact skin and a constant dose of drug is absorbed. Two different patches have been developed; a reservoir patch and a matrix patch. These patches differ in the way fentanyl is stored. However farmacokinetically, they are comparable . Nowadays, only the matrix patch is used in clinical practice.

After placement of the patch, the plasma fentanyl concentration gradually increases. After 72hrs the patch has to be changed for a new one, as a stable diffusion of the drug through the skin is no longer guaranteed. Steady state concentrations are approached when a second transdermal fentanyl patch is sticked on the skin . Removing the patch will not immediately lead to diminished fentanyl concentrations because of the amount of fentanyl stored in subcutaneous depots, and therefore systemic concentrations will gradually decrease.

Fentanyl is a drug that is highly lipophilic and binds strongly to plasma proteins. Fentanyl is more potent than morphine at equipotent dose levels . The metabolism of fentanyl takes place primarily in the liver . Fentanyl is mainly oxidized into the inactive metabolite norfentanyl by the CYP3A4 iso-enzyme . Less than 1% is metabolized to despropionyl-fentanyl, hydroxyfentanyl, and hydroxynorfentanyl, which are also inactive metabolites. Fentanyl is mainly excreted renally and for a minor part through the feces. The large majority of the fentanyl is excreted as the metabolites mentioned; 10% as unchanged drug .

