The polycyclic aromatic hydrocarbons in cigarette smoke are believed to be responsible

for the induction of cytochrome P450.. A study with erlotinib showed a significantly decreased AUC in smokers compared to nonsmokers . Both erlotinib and fentanyl are mostly metabolized by CYP 3A4. A small part of the metabolism of erlotinib is also influenced by CYP 1A1. Cigarette smoke induces CYP 1A1 and can lead to a cascade, which also involves CYP 3A4, thereby influencing the clearance of erlotinib . Probably, it also influences the metabolism of fentanyl. A study from our group with irinotecan showed a lower exposure to SN-38 (the active irinotecan metabolite) in smokers compared to non-smokers. The hypothesis was that irinotecan is highly sensitive to CYP3A induction and that this is modulated by cigarette smoking .. Possible influence of smoking on clearance of fentanyl is important to know. Terminally ill patients often change their habits in the last part of life. Heavy smokers are physically not able to smoke as much as they did before, or occasional smokers smoke more because of stress. Both scenarios can potentially influence the fentanyl clearance. This may result in over- or underdosing of fentanyl, causing intoxication or ineffective pain treatment.

As a result of these earlier publications, in this study we want to determine which patient characteristics influence the pharmacokinetics of fentanyl.

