# OBJECTIVES

Primary Objective:

- to study the effect of BMI on pharmacokinetics of fentanyl by comparing the AUC between patients with a BMI < 20 and patients with a a BMI > 25, both using a stable dose of the fentanyl patch (Durogesic ®).

Secundary Objective:

- to study the effect of smoking on pharmacokinetics of fentanyl by comparing the AUC between smokers and non-smokers, both using a stable dose of the fentanyl patch (Durogesic ®).

Stable dose is defined as using the same dose of fentanyl during at least 8 days.

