# STUDY DESIGN

This is a single-center pharmacokinetic cohort study. The trial will be performed at the Erasmus MC Cancer Institute, department of Medical Oncology.

Patients with a stable dosage of fentanyl used through a patch can be included. Stable dose is defined as at least 8 days using a stable fentanyl dosage. Blood samples are always taken on the 2nd day of the used patch.

Patients will be asked to stick a fentanyl patch (Durogesic ®) during 3 periods at the upper arm. During the third period, a venous blood sample will be taken. This blood sample will be taken at the same moment as a regular blood sampling is performed.

After taking the blood sample the patient has finished the study.

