## Sample size calculation

BMI

With a suggested inter-patient variability in fentanyl pharmacokinetics of 25%, a power of 0.8 and two-side testing (P <0.025) at least **20 evaluable patients** in each group are required to determine a difference in exposure between the two BMI-groups of 25%. To evaluate the differences in plasma fentanyl concentrations the Student’s t test is used. Smokers and non-smokers will be distributed equally in these BMI-groups.

Smoking

Around 25% of the Dutch population smokes. In this study at least 20 patients have to be smokers and at least 20 have to be non-smokers to detect a similar difference in exposure of 25%. Patients can be included independently of their BMI. Smokers are patients who are smoking daily any kind of tobacco or e-cigarettes. Non-smokers are patients who quit smoking at least one month before PK sampling.

In conclusion, the cohort exists of:

- At least 20 patients with BMI < 20 (about 5 smokers)
- At least 20 patients with BMI > 25 (about 5 smokers)
- At least 20 patients defined as smokers
- At least 20 patients defined as non-smokers
- Dependent on the number of smokers in the extreme BMI groups: about 40 patients with

20 ≤ BMI ≤ 25 (about 10 smokers)

In total we will include a maximum of 80 patients.

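### The unadjusted comparison of clearance between BMI groups cannot separate BMI from liver function or albumin, and the protocol does not provide for recording either

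*Protocol*

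**What the plan says.** Section 2 of the protocol (Objectives) sets out "to study the effect of BMI on pharmacokinetics of fentanyl by comparing the AUC between patients with a BMI < 20" with patients above 25. Section 10 (Statistical analysis) names clearance as the quantity tested and a Student's t test as the method: "we will use the Student’s t test to compare the clearance for fentanyl in patients with a BMI < 20 compared to a BMI >", where the upper cut-off is 25. It names no covariate.

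Section 1 (Introduction and rationale) supplies two pharmacological facts that bear on this contrast: "Fentanyl is a drug that is highly lipophilic and binds strongly to plasma proteins", and "The metabolism of fentanyl takes place primarily in the liver". The same section gives subcutaneous fat as the expected mechanism, with higher concentrations at higher BMI, and closes with a wider aim: "in this study we want to determine which patient characteristics influence the pharmacokinetics of fentanyl".

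Two other influences on elimination are controlled. Strong cytochrome P450 inhibitors and inducers are excluded (section 4.3), and smokers are to be spread equally over the BMI groups (section 4.4). Liver function, albumin and extent of disease appear nowhere as an eligibility criterion, a balancing factor, a recorded variable or a covariate. The endpoints in section 8.1 are pharmacokinetic only, and sections 8.1.3 and 10.3 (other parameters) are marked as not applicable.

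Section 3 (Study design) says of the study sample: "This blood sample will be taken at the same moment as a regular blood sampling is performed".

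**The concern.** Patients are recruited at a medical oncology outpatient department, and BMI is observed, not assigned. Patients with BMI <20 may differ from those with BMI >25 in more than subcutaneous fat. If more of them have impaired liver function, their clearance would be lower for that reason alone. Altered protein binding could also move total concentration, and the documents do not say in which direction or by how much.

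The hypothesis in section 1 implies lower exposure, and so higher apparent clearance, at low BMI. Poorer liver function in the low-BMI group would push the other way. It could hide a true difference, or produce an apparent one in the opposite direction where BMI has no effect. This would happen even with smoking perfectly balanced, and a larger sample would not remove it.

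A later statistical analysis plan could add a model. It could not be relied on to adjust for values that the protocol never provides for collecting.

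**Working it through.** **1. The plan's own figure.** Inputs from section 4.4: variability 25% (taken as SD 0.25 of the mean), difference 25%, and "a power of 0.8 and two-side testing (P <0.025").

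n per group = 2 × (z₀.₉₈₇₅ + z₀.₈₀)² × (SD/difference)² = 2 × (2.241 + 0.842)² × (0.25/0.25)² = 19.01, rounded up to **20**.

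The stated 20 per group is reproduced. Power at 20 per group is 0.82 by the normal approximation and 0.79 by the noncentral t. This calculation covers random error only.

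**2. Size of a possible bias.** The documents give no figures, so these inputs are assumptions: impaired liver function in 20-40% of the BMI <20 group and 10% of the BMI >25 group, raising exposure by 20-50%.

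- Bias on exposure = (difference in prevalence) × (relative rise in exposure).
- Section 10 tests clearance. At a given dose rate clearance is inversely proportional to exposure, so a rise r in exposure is a fall of 1 − 1/(1 + r) in clearance: 20% → 16.7%, 40% → 28.6%, 50% → 33.3%.
- Bias on clearance = (difference in prevalence) × (fall in clearance), as a share of the mean with normal liver function.

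| Assumed case | Bias on exposure | Bias on clearance |
|---|---|---|
| 20% v 10%, exposure +20% | 0.10 × 20 = 2 points | 0.10 × 16.7 = 1.7 points |
| 30% v 10%, exposure +40% | 0.20 × 40 = 8 points | 0.20 × 28.6 = 5.7 points |
| 40% v 10%, exposure +50% | 0.30 × 50 = 15 points | 0.30 × 33.3 = 10.0 points |

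On clearance, the middle case is 5.7/25 = 23% of the design difference and the upper case is 10/25 = 40%.

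**3. Effect on the planned test** (noncentral t, 20 per group, SD 0.25, two-sided 0.025, clearance scale). The last column applies the shift against a true difference of 25 points.

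| Shift in clearance | Rejection rate, no BMI effect (nominal 2.5%) | Power when the shift opposes the true difference (0.79 without shift) |
|---|---|---|
| 1.7 points | 2.8% | 0.73 |
| 5.7 points | 6.3% | 0.55 |
| 10.0 points | 15% | 0.34 |

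**4. Price of adjustment.** With one covariate, the SD of the contrast is multiplied by √[(1 − R²)/(1 − r²)], where r is the correlation of the covariate with BMI group and R its correlation with clearance. Both are assumed. Power is by the normal approximation at 20 per group.

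| r | R | Power | n per group for 0.80 |
|---|---|---|---|
| 0.3 | 0.3 | 0.82 | 20 |
| 0.5 | 0.5 | 0.82 | 20 |
| 0.5 | 0.3 | 0.74 | 24 |
| 0.7 | 0.3 | 0.55 | 34 |

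One covariate fits roughly within the planned size unless it is strongly correlated with BMI group.

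**The case against.** **The protocol lists endpoints, not baseline data.** The endpoint sections do not list BMI or smoking status either, although both define the groups. Their silence therefore does not prove that liver tests or albumin would go unrecorded. This stands. The supportable statement is that the protocol does not provide for recording them.

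**BMI <20 as a marker of advanced disease.** A reader might infer this, but no section says so. Section 1 speaks of cachexia for groups with mean BMI 16 or BMI ≤18.5, both stricter than this study's cut-off, and the patients here are outpatients on a stable dose. The link is plausible but remains an inference.

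**Kidney function.** Section 1 says that fentanyl is excreted mainly by the kidney, which invites adding renal function to the list. The same section says that most is excreted as inactive metabolites and 10% as unchanged drug, so it gives little ground for renal function as a major confounder of parent-drug clearance.

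**An uninterpretable result.** It is tempting to say that any finding would be uninterpretable. The documents do not support that. Hepatic confounding of the assumed kind works against the hypothesised direction, so a positive result in that direction would appear despite it. At the low end of the assumed range the harm is negligible.

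**Exploratory aim.** The summary calls the study explorative and speaks of a relation, and section 1 wants to predict who is at risk of under- or overdosing. An unadjusted association is useful for prediction. This softens the point but does not remove it, because section 2 says effect and section 1 also asks which patient characteristics matter.

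**Loss of an effect on adjustment.** One might conclude that a BMI effect which disappears on adjustment was never due to BMI. With about 40 patients that does not follow. Precision may simply be lost, and albumin may share the nutritional pathway with BMI, so adjusting for it could remove part of the association of interest.

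**Conclusion.** The point holds as a cheap improvement. An unadjusted t test between non-randomised BMI groups of oncology outpatients is a weak basis for a statement about the effect of BMI when the protocol's own pharmacology names liver metabolism and protein binding, and neither liver function nor albumin is restricted, balanced, recorded or adjusted for.

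Under the assumed prevalences and effects, the bias is about 2-15 points on exposure, or about 2-10 points on the clearance scale actually tested. The rejection rate with no BMI effect is then about 3-15% against 2.5% nominal. All of this depends on assumed inputs and on the inference that low BMI goes with more disease. The effect of altered protein binding is not quantified. The sample size of 20 per group is not in question here.

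**What to change.** - **Section 8.1.3:** in place of not applicable, record albumin, bilirubin and transaminases where available from the regular blood draw, and presence of liver metastases from the patient file.
- **Section 10:** keep the t test. Tabulate these values by BMI group. Add one prespecified supporting model of log clearance on BMI group, adjusted for a liver-function measure, with albumin added as a further sensitivity analysis.
- **Reporting:** give the BMI estimate and confidence interval with and without adjustment. If they differ materially, word the result as an association not separable from disease status. Do not adopt a rule that an effect lost on adjustment is not due to BMI.

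**Cost:** copying routine values into the study record and fitting the supporting models, with no extra visit or blood draw. Some values will be missing where a test was not ordered that day. With about 40 patients in the comparison, some precision is lost if BMI group and the covariate are strongly correlated.

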**SUMMARY**

**Rationale:** Fentanyl is a strong opioïd and is highly lipophilic. Fentanyl pharmacokinetics are characterised by large inter- and inpatient differences, which may have serious consequences for the activity and toxicity profile of this drug. In this study we explore the influence of BMI and smoking behaviour on the pharmacokinetics (i.e. clearance (CL)) of fentanyl.

**Objective:** Primary objective: To study the relation between BMI and the pharmacokinetics of fentanyl, in patients using a stable dose of the fentanyl patch (Durogesic ®). Secundary objective: to study the relation between smoking and the pharmacokinetics of fentanyl, in patients using a stable dose of the fentanyl patch (Durogesic ®).

**Study design:** explorative cohort study

**Study population:** All patients using a stable dose of a fentanyl (Durogesic ®) patch (for at least 8 days).

**Intervention (if applicable)**: not applicable

**Main study parameters/endpoints:** Pharmacokinetics (Clearance, AUC, etc.)

**Nature and extent of the burden and risks associated with participation, benefit and group relatedness:** This study has an **extremely low** risk for the participating patients. After taking 1 blood sample, the study is finished. There is no direct benefit for the patient.

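### The two unadjusted t tests leave any smoking imbalance between the BMI groups uncorrected and lose power even at balance; the BMI contrast should be adjusted for smoking, and the smoking contrast for BMI

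*Protocol*

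**What the plan says.** Section 10 (Statistical analysis) calculates a clearance for each sample; Student's t test then serves "to compare the clearance for fentanyl in patients with a BMI < 20 compared to a BMI > 25 and for smokers versus non-smokers". No covariate, stratification or model is named. Section 4.4 (Sample size calculation) also names the t test.

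The primary objective in section 2 (Objectives) is an extreme-group contrast, "comparing the AUC between patients with a BMI < 20 and patients with a a BMI > 25". The Summary words the aim more broadly: "To study the relation between BMI and the pharmacokinetics of fentanyl".

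Section 4.4 plans at least 20 patients with BMI <20 and at least 20 with BMI >25, about 5 smokers in each, and states that smokers are to be spread evenly over these groups. For the smoking comparison, "Patients can be included independently of their BMI". The middle stratum (BMI 20 to 25, about 10 smokers) is sized conditionally: "Dependent on the number of smokers in the extreme BMI groups: about 40 patients with". The total is at most 80.

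Section 1 (Introduction and rationale) hypothesises higher concentrations at higher BMI, and expects smoking to influence fentanyl metabolism, citing lower exposure in smokers for two other drugs.

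**The concern.** Two non-randomised traits are each expected to move the same outcome, and each is tested as if the other did not exist. This has two consequences.

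- **Imbalance.** If smokers are unevenly spread over the two extreme BMI groups, part of any smoking effect is reported as a BMI effect. More smokers in the low-BMI group would exaggerate the hypothesised BMI effect; more in the high-BMI group would mask it. The even spread in section 4.4 is an intention with approximate counts. No quota or other mechanism is described, and the conditional size of the middle stratum shows that the number of smokers in the extreme groups is expected to vary.
- **Noise.** Even with identical smoking proportions, an unadjusted test leaves the smoking effect in the within-group variance. The enrolment ceiling, which section 8.5 attributes to funding, means this cannot be recovered by adding patients.

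**Working it through.** **1. The protocol's own figure.** Inputs from section 4.4: SD 25%, difference 25%, power 0.8, "two-side testing (P <0.025").

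n per group = 2 × (2.241 + 0.842)² × (0.25/0.25)² = 19.01, rounded up to 20. The stated 20 reproduces. This calculation contains no smoking effect.

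**2. Expected confounding at plan.** Planned smokers are 5/20, 10/40 and 5/20, which is 25% in every BMI group. The shift in the BMI contrast is (difference in smoking proportion) × (smoking effect) = 0.

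**3. How far chance could move the balance.** Assume no balancing is enforced and smokers arrive independently at 25%. For two Binomial(20, 0.25) counts, the difference is:

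| Difference in smokers | Probability |
|---|---|
| 3 or more | 36% |
| 4 or more | 20% |
| 6 or more | 4% |

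**4. Power at exact balance (5/10/5).** Assumptions not in the protocol: log scale, where clearance and dose-normalised exposure differ only in sign; BMI ratio 1.25 between the extreme groups; smokers 25% lower.

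- Residual variance: ln(1 + 0.25²) = 0.0606, SD 0.246. SE of the difference = 0.246 × √(2/20) = 0.0779. Target difference ln(1.25) = 0.2231.
- Variance added within each group by smoking: 0.25 × 0.75 × (ln 0.75)² × 20/19 = 0.0163. The t test therefore estimates a variance of 0.0770 and an SE of 0.0877.
- Unadjusted t test (38 df, critical value 2.334): it must exceed 2.334 × 0.0877 = 0.2048. Power ≈ Φ((0.2231 − 0.2048)/0.0779) = Φ(0.24) ≈ 0.59.
- Three BMI groups plus smoking on 80 patients (76 df, critical value 2.287): it must exceed 2.287 × 0.0779 = 0.1781. Power ≈ Φ((0.2231 − 0.1781)/0.0779) = Φ(0.58) ≈ 0.72. Simulation gives 0.71 to 0.72.
- No smoking effect: simulated power is about 0.69 to 0.70 unadjusted and 0.71 to 0.72 adjusted, so adjustment costs nothing.

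The adjusted group contrast does not depend on the shape of the BMI effect. Its simulated power is 0.71 to 0.73 under a step at BMI 20, a step at BMI 25, or equal steps at both, against 0.58 to 0.60 for the t test.

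**5. Type I error under imbalance.** Simulated, no BMI effect, smokers 25% lower, nominal 2.5%:

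| Smokers, low vs high BMI | Spurious difference, exp(gap/20 × 0.2877) − 1 | t test rejects | Adjusted model rejects |
|---|---|---|---|
| 5 vs 5 | 0% | about 1% | about 2.5% |
| 6 vs 4 | 3% | 1.4 to 2% | about 2.5% |
| 7 vs 3 | 6% | about 4% | about 2.5% |
| 8 vs 2 | 9% | about 8% | about 2.4% |

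The t test is conservative near balance because smoking inflates its variance estimate; it becomes anti-conservative as the gap grows. In the other direction, with 2 vs 8 smokers and a true ratio of 1.25, its power falls to 0.22, against 0.69 for the adjusted model.

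**The case against.** Four counter-arguments deserve weight.

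- **Balance is planned.** A reader might infer that the design confounds BMI with smoking. It does not: section 4.4 plans equal smoking proportions, and admitting patients to the smoking comparison regardless of BMI is an eligibility statement, not evidence of imbalance. What remains is that the balance is approximate, unenforced on paper, and has no analytic fallback.
- **The severe error rate is a stress case.** Even without balancing, a gap of six or more smokers occurs in about 4% of trials, and at 6 vs 4 the t test stays below its nominal level. This stands, so the main argument is the power loss at balance plus protection against moderate gaps.
- **The middle stratum is not wasted.** A reader might infer from the Summary that leaving out BMI 20 to 25 contradicts the objective. Section 2 states the extreme-group contrast, the t test matches it, and the middle patients serve the smoking comparison. The figures are also about 40 and at most 80, not fixed.
- **A linear BMI term is not simply better.** It is tempting to replace the contrast with continuous BMI on all patients. Under a linear effect that model has power of about 0.80, but under a step at BMI 20 it falls to about 0.51, against about 0.60 for the plain t test. A threshold is plausible from section 1: a difference was seen at mean BMI 16, but none in two studies whose lowest group was BMI 18.5 or below.

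A covariate for time since patch application is also tempting, because section 3 says only "Blood samples are always taken on the 2nd day of the used patch". The protocol does not say that clock times are recorded, and the effect of such a term has not been evaluated here. It is a separate matter.

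The study is exploratory and a separate analysis plan may add adjusted analyses. The protocol text nevertheless fixes the unadjusted tests.

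**Conclusion.** The point holds in a limited form. The fixed analysis ignores a factor that the protocol itself expects to matter and already needs to record. There is no built-in bias at the planned counts. The cost at exact balance is a drop in power from about 0.71 to 0.59 if smoking has the 25% effect the protocol targets, and almost nothing if smoking has no effect. Under imbalance the test can report a spurious BMI effect or hide a real one; the size runs from negligible at 6 vs 4 smokers to about 8% false rejections at 8 vs 2.

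These figures rest on log-normal data with the protocol's 25% CV, a ratio of 1.25, a 25% lower exposure in smokers, 20/40/20 patients and two-sided 0.025. For the smoking comparison the gain is small: about 0.92 unadjusted and 0.94 adjusted, taking 20 smokers and 60 non-smokers, effects of one SD, and a linear BMI effect over assumed BMI ranges of 16–20, 20–25 and 25–32.

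**What to change.** In section 10, replace the two t tests with one linear model on all evaluable patients, with BMI group (<20, 20 to 25, >25) and smoking status as terms.

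- Primary result: the BMI <20 versus >25 contrast from this model, at the stated significance level, with a confidence interval.
- Secondary result: the BMI-adjusted smoking effect from the same model.
- Supporting analysis: continuous BMI plus smoking on all patients, with linearity checked, to address the relation named in the Summary.

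Align the t-test sentence in section 4.4 with this. The 20 per group can stay as the planning basis. State how the even spread of smokers will be achieved, or say that it is only a target and that the model handles departures.

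Cost: a change of wording and slightly more analysis work. No new data are needed, because BMI and smoking status are already required for group assignment.
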